**Methods:**

A three-arm prospective randomized open-label study with a parallel group design will be used. A total of 25 female adolescents with JIA who have pain will be randomized in a ratio of 2:2:1 to one of the 3 groups: (1) online yoga training program (group A: n=10); (2) online aerobic dance training program (group B: n=10); and (3) electronic pamphlet control group (group C: n=5). Participants in groups A and B will complete 3 individual 1-hour sessions per week using online exercise videos, as well as a 1-hour virtual group session per week using a videoconferencing platform for 12 weeks. Participants from all groups will have access to an electronic educational pamphlet on PA for arthritis developed by the Arthritis Society. All participants will also take part in weekly online consultations with a research coordinator and discussions on Facebook with participants from their own group. Feasibility (ie, recruitment rate, self-reported adherence to the interventions, dropout rates, and percentage of missing data), acceptability, and usability of Facebook and the videoconferencing platform will be assessed at the end of the program. Pain intensity, participation in general PA, morning stiffness, functional status, fatigue, self-efficacy, patient global assessment, disease activity, and adverse events will be assessed using self-administered electronic surveys at baseline and then weekly until the end of the 12-week program.

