### Objectives

The primary objectives of the proposed single-blind three-arm pilot RCT with a parallel group will be to examine (1) the feasibility of a 12-week full-effectiveness trial of two popular types of PA and an electronic pamphlet control group: group A: an online yoga training program and a PA electronic educational pamphlet; group B: an online aerobic dance training program and a PA electronic educational pamphlet; group C: an electronic pamphlet control group (PA electronic educational pamphlet) postintervention; and (2) the acceptability of the yoga and aerobic dance PA interventions. The secondary objective of this pilot RCT will be to examine the initial effectiveness of a yoga training program (group A) and an aerobic dance training program (group B) on pain intensity, participation in PA, morning stiffness, functional status, self-efficacy, fatigue, patient global assessment, disease activity, and adverse events in female adolescents (aged 13 to 18 years) with JIA compared with an electronic pamphlet control group (group C) postintervention.

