### Interventions

#### Group A

Participants assigned to this group will be invited to complete a yoga training program. The yoga training program, an evidence-based educational program, is a structured low-intensity Vishwas Raj [26]. This yoga program consists of stretching, strengthening, meditation, and deep breathing and has been shown to be acceptable and effective among adults with RA. Participants will be asked to complete 3 individual 1-hour sessions per week for 12 consecutive weeks by watching a previously filmed session led by a qualified yoga instructor and posted on Facebook. They will also take part in a 1-hour virtual group session per week using a video-conferencing platform. Participants will also participate in weekly online consultations with a research coordinator and discussions on Facebook with other participants in group A. Finally, participants will receive an electronic pamphlet on physical exercise developed by the Arthritis Society. The electronic pamphlet, which groups B and C will also receive, explains how PA can help manage arthritis. It includes valuable tips and a detailed list of the various types of PA and exercises.

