### Participant Allocation

Once informed consent is obtained, participants will be randomly assigned to one of the 3 groups using the central randomization scheme [60] and based on a sequence of computer-generated random numbers using a blocking factor (randomly varying between 6 and 9). The central stratified randomization process will be based on age (between 13 and 15 years and between 16 and 18 years).

Before running the randomization program, the data manager will document the participant’s initials (first and last names) and date of birth (month and year). After running the program, the data manager will prepare sealed opaque envelopes with the group allocation and study ID number for each patient and will provide it to the research coordinator. Participants will open the sealed opaque envelope containing their group assignment and a confidential link to access their Facebook group page where further instructions can be found. The research coordinator will explain the procedures related to the group assigned and will ask participants to indicate their availability for an initial individual online consultation as well as for virtual group sessions. Participants will be asked not to change their usual level of PA during the study except for following the program to which they were assigned.

At the clinic, participants will complete a questionnaire that will gather the following information:

Sociodemographic information: partial date of birth (month/year), age, gender, ability to understand English, and ability to use and access the internet weekly for the study duration.Medical information: diagnosis, partial date of diagnosis (month/year), disease duration, presence of serious chronic diseases (eg, cancer or other illnesses) or cognitive impairments, presence of contraindications to exercise (as determined by the treating rheumatologist), current use of JIA-specific medication, anticipated change in JIA-specific medication in the next 12 weeks, and use of physical interventions/treatments other than the prescribed medication for JIA pain relief and pain level when performing regular activities. A chart review will help verify this information.PA information: the amount of PA performed weekly using a validated exercise log [61] and preferences in terms of PA (eg, yoga, Zumba, or other types).

At baseline, all the participants will be asked to do the following:

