Group C: Participants will be invited via Facebook and email to attend an individual online consultation with the research coordinator using a video-conferencing platform. During this consultation, participants can ask questions related to their group assignment, voice their concerns, and discuss PA in general and their plan for PA in the future. They will also be invited to consult the electronic pamphlet on PA each week. For the remainder of the study duration, participants will be encouraged to attend, when possible, individual weekly 10-min online consultations. During these consultations, participants can discuss their use of PA, as well as facilitators and barriers to participating in PA. Participants will be asked to record their PA using a validated exercise log [61] as well as their pain intensity and fatigue by completing a brief electronic questionnaire that regroups valid instruments on a weekly basis.

Throughout the study, the Facebook pages will provide a means of communication for participants who will be able to share their experiences, post comments on the videos, and ask questions of each other and the research coordinator. Access to Facebook group pages will be restricted to study participants. Adolescents who cannot or do not want (or are not granted parental permission) to access Facebook will be given a link to the CHEO webpage that will contain information related to the study and their group. However, they will not be able to interact (ie*,* leave comments or questions) using this platform.

At 6 and 12 weeks, all participants will be asked to complete online questionnaires about the program that they were allocated to as well as the acceptability of Facebook to deliver PA programs. They will also be asked if they used any other PA during the study. They will also complete online questionnaires assessing their pain intensity, functional status, fatigue, self-efficacy, and well-being (using a patient global assessment). This will take about 20 to 30 minutes to complete.

As a compensation for the time given by participants, they will receive a US $21.40 gift certificate for completing baseline questionnaires and a US $21.40 gift certificate for completing postintervention questionnaires. They will also receive a personalized certificate of participation (community hours for school).

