Feasibility will be assessed by the recruitment rate, the randomization process, and self-reported adherence and measured using a questionnaire, as well as protocol deviations, dropout rates, and percentage of missing data in the questionnaires.Recruitment rate: The number of participants recruited in the trial and the time used for recruitment will be documented in a feasibility form. The number of participants will be divided by the duration of recruitment. This will be measured on a continuous basis for up to 12 weeks.Randomization process: The ease at which the randomization process is conducted will be described by researchers in a feasibility form. This will be measured on a continuous basis for up to 12 weeks.Number of protocol deviations: The number of protocol deviations, the time at which they occur, the group in which they occur, and the potential reasons for these will be documented in a feasibility form. Participants will be asked why they deviated from the protocol by researchers using a feasibility form. This will be measured on a continuous basis for up to 12 weeks.Dropout rates: The number of participants who dropped out of the trial, the time at which they dropped out, the group in which they belonged, and the reasons for these will be documented in a feasibility form. Participants will be asked why they dropped out by researchers. The number of dropouts in each group will be divided by the duration of the trial. This will be measured on a continuous basis for up to 12 weeks.Percentage of missing data in the questionnaires: The percentage of missing data in the questionnaires, the time at which they occur, and potential reasons for these will be documented in a feasibility form. This will be measured on a continuous basis for up to 12 weeks.Self-reported adherence: Self-reported adherence to the training programs will be assessed by monitoring the number and length of sessions and dividing the time spent performing the program by the duration of prescribed sessions of either yoga or aerobic dance. Self-reported adherence will be recorded weekly using an adapted online version of the validated 7-day PA Report calendar (in minutes) [62]. This will be measured each week for up to 12 weeks.The acceptability of the yoga or aerobic dance interventions will be assessed using a questionnaire-administered postintervention. Questions will explore the acceptability of online consultations, virtual group sessions, PA videos (either yoga or aerobic dance programs), electronic pamphlet, and training programs (content and duration of the yoga and aerobic dance programs), as well as facilitators and barriers to participating. This questionnaire will be administered at 6 and 12 weeks.The usability of Facebook will be assessed by the System Usability Scale (SUS) [63,64]. The SUS is composed of 10 items using a 5-point scoring system ranging from Strongly Disagree (a score of 1 out of 5 for each question) to Strongly Agree (a score of 5 out of 5 for each question). The total score ranges from 5 (low usability) to 50 (high usability). The usability will be measured at 6 and 12 weeks.The usability of the videoconferencing platform will be assessed by the SUS [63,64]. The SUS is composed of 10 items using a 5-point scoring system ranging from Strongly Disagree (a score of 1 out of 5 for each question) to Strongly Agree (a score of 5 out of 5 for each question). The total score ranges from 5 (low usability) to 50 (high usability). The usability will be measured at 6 and 12 weeks.The use of Facebook will be assessed by the number of posts, live online discussions, and views of the videos. The use will be measured at 6 and 12 weeks.

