
The following outcome measures will be used to answer the secondary objective:

*Pain intensity* will be assessed using the electronic Childhood Health Assessment Questionnaire (CHAQ) 100-mm pain VAS subscale [65]. It uses a scoring system where 0 mm represents no pain and 100 mm represents very severe pain the past week. This measure has already been validated in the JIA population [65,66]. Pain intensity will be measured at baseline, 6 weeks, and 12 weeks.*Participation in PA (level of PA)* will be assessed by using the electronic Physical Activity Questionnaire for adolescents (PAQ-A) aged 14 to 18 years, a 7-day recall instrument measuring the level of PA within the last 7 days [67-69]. The PAQ-A is composed of 8 items using a 5-point scoring system. The total score is calculated by taking the mean score out of 5, with 1 indicating low PA and 5 indicating high PA. The PAQ-A has been reported to be a valid and reliable measure of general PA levels in youths and adolescents [67-69]. Participation in PA will be measured at baseline, 6 weeks, and 12 weeks.*Participation in PA (duration and intensity)* will be assessed by using an exercise log, based on the 7-day PA Recall calendar [62], which will be used weekly. The PA level will be reported in terms of minutes and intensity levels (3 subscales: moderate, hard, and very hard intensity; subscale total scores in minutes) and will be transformed into the metabolic equivalent of tasks, which are units of the basal metabolic rate and express the energy cost of PA. Participation in PA will be measured at baseline, 6 weeks, and 12 weeks.*Morning stiffness* will be assessed by using electronic self-reported questions asking about the presence (Yes/No) and duration of morning stiffness in minutes. It will be measured at baseline, 6 weeks, and 12 weeks.*Functional status* will be assessed using the electronic CHAQ. The CHAQ contains 8 domains (dressing/grooming, arising, eating, walking, hygiene, reach, grip, and activities), and items are scored using a 4-point Likert scale of 0 to 3, where 0 represents the ability to perform the activity with no difficulty, 1 represents the ability to perform with some difficulty, 2 represents the ability to perform with much difficulty, and 3 represents the inability to perform over the past week. The mean of the 8 scores will determine the total CHAQ score ranging from 0 to 3, with a lower score indicating higher functional status and a higher score indicating lower functional status. It is the most widely used functional health status measure in JIA, which is a reliable and valid tool for the functional, physical, and psychosocial assessment of children with JIA [65]. It will be measured at baseline, 6 weeks, and 12 weeks.*Fatigue* will be assessed by using an electronic version of a subset of the Patient-Reported Outcomes Measurement Information System Pediatric Short Form version 1.0—Fatigue 10a [70], which measures fatigue and its impact, scored from 1 to 5, where 1 represents never tired and 5 represents almost always tired in the past week. It will be measured at baseline, 6 weeks, and 12 weeks.*Self-efficacy* will be assessed by using the Children’s Arthritis Self-Efficacy Scale (CASE), a specific, valid and reliable tool for JIA [71]. CASE is an 11-item self-report scale that is divided into 3 concepts: activity, symptom, and emotion. A 5-point Likert scale is used to rate responses for each item, where 1 represents not at all sure and 5 represents very sure based on the confidence of the child to manage disease effects. It will be measured at baseline, 6 weeks, and 12 weeks.*Patient Global Assessment* will be assessed by using an item used in the Juvenile Arthritis Quality of Life Questionnaire (JAQQ). JAQQ was designed to assess HRQOL in children aged 2 to 18 years JIA or juvenile spondylarthritides [72-75]. JAQQ includes 4 subscales (gross motor function, fine motor function, psychosocial function, and systemic symptoms) as well as a pain and patient global assessment. The patient global assessment asks how youths have been since the last assessment (prior week) on a 5-point Likert scale, scored from 1 to 5, where 1 represents much better and 5 represents much worse. It will be measured at 6 weeks and 12 weeks.*Disease activity* will be assessed by using the active joint count, the number of joints with active disease according to the rheumatologist [1].Adverse events will be reported by participants in answers to open questions.

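### The physical-activity outcome does not separate assigned sessions from other activity, which participants are asked to hold constant, and it is unclear what following the program means for group C

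*Protocol article*

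**What the plan says.** **The instruction.** Under Participant Allocation, every participant is given the same request: "Participants will be asked not to change their usual level of PA during the study except for following the program to which they were assigned".

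**The outcome.** The secondary objective (Objectives) is the initial effectiveness of yoga and dance against the pamphlet group "on pain intensity, participation in PA, morning stiffness, functional status, self-efficacy, fatigue, patient global assessment, disease activity, and adverse events". The abstract words the PA item more broadly: "Pain intensity, participation in general PA, morning stiffness".

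**The instruments.** Outcome Measures names two. The PAQ-A is described as "a 7-day recall instrument measuring the level of PA within the last 7 days". Duration and intensity "will be assessed by using an exercise log, based on the 7-day PA Recall calendar [62], which will be used weekly", scored in minutes on three subscales that begin at moderate intensity. Neither description says whether assigned yoga or dance sessions count.

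**Adherence.** The same section takes this feasibility measure from a source with the same reference number as the log: "Self-reported adherence will be recorded weekly using an adapted online version of the validated 7-day PA Report calendar (in minutes) [62".

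**Group C.** This group has no assigned exercise sessions. It receives a pamphlet that "explains how PA can help manage arthritis. It includes valuable tips and a detailed list of the various types of PA and exercises", is invited each week to consult it, and has consultations in which participants can "voice their concerns, and discuss PA in general and their plan for PA in the future". Later weekly consultations cover their use of PA and what helps or hinders it.

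**The concern.** An effectiveness outcome called general PA should tell the reader whether an adolescent offered yoga or dance becomes more active. Here, activity outside the program is meant to stay flat by request, and activity inside the program is the intervention itself. If the two are added together, the A–C and B–C differences are hard to distinguish from session attendance, which is already reported as adherence. A pilot reader could then take a PA gain as a behavioural effect and carry it into the full-scale trial.

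The second issue is what group C is being asked to do. The request exempts the assigned program, but the article does not say whether becoming more active on the pamphlet's advice falls within that exemption. Protocol deviations are counted by group as a feasibility measure, so the answer bears on a primary outcome as well as on how the comparator is described.

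**Working it through.** The plan gives no figure for the size of the PA contrast, so there is nothing to reproduce. The check is arithmetic on the prescription, followed by a comparison of the sections.

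**Inputs**
- Groups A and B: three individual 1-hour sessions plus one 1-hour group session a week for 12 weeks (Interventions).
- Group C: no assigned sessions (Interventions, Group C).
- Intensity: yoga low, dance low to moderate (Interventions). The log has no subscale below moderate (Outcome Measures).
- Adherence and the share of session time that reaches moderate intensity are not given. Both are varied below as assumptions.

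**Step 1: prescribed time.** 3 × 60 + 1 × 60 = 240 min/week, and 240 × 12 = 2,880 min over the study.

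**Step 2: what the log difference contains.** Let *a* be adherence, *s* the share of session time scored as moderate or above, and ΔO the change in other PA. If sessions are logged:

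D = a × s × 240 + (ΔO in A or B − ΔO in C)

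If the request is followed and group C takes it as covering all its activity, both ΔO terms are zero and D = a × s × 240.

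| Adherence | s = 1 | s = 0.5 | s = 0 |
|---|---|---|---|
| 100% | 240 | 120 | 0 |
| 75% | 180 | 90 | 0 |
| 50% | 120 | 60 | 0 |
| 25% | 60 | 30 | 0 |

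(min/week)

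For dance, *s* may lie anywhere from 0 to 1, so 240 is an upper limit. For yoga, *s* may be close to 0. The same attendance could therefore give a large log difference in group B and almost none in group A.

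If sessions are not logged, the first term drops out and the request itself asks for D = 0.

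**Step 3: can D be interpreted?** A difference of 120 min/week could come from full adherence with half the time at moderate intensity (1 × 0.5 × 240), from half adherence with all of it at moderate intensity (0.5 × 1 × 240), or from no attendance and 120 more minutes of other PA. Total minutes alone do not distinguish these. The PAQ-A is a mean score from 1 to 5 and cannot be split into minutes at all.

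**Step 4: group C.** Two readings of the request fit the text.
- *Acting on the pamphlet is allowed.* Later in Participant Allocation, all participants are asked at 6 and 12 weeks about the program they were allocated to. Group C therefore has a program, and the pamphlet is part of it.
- *Acting on the pamphlet is a departure.* The Group C section describes talk about past activity, the pamphlet and future activity, which fits activity staying stable during the 12 weeks.

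With 5 participants in group C, each one classified the other way moves the proportion with a deviation by 1/5 = 20 percentage points.

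**The case against.** Several points on the other side stand.

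- Asking everyone to keep outside activity stable is ordinary control of co-interventions. It applies equally to all arms and protects the pain, function and fatigue contrasts.
- Total PA is a legitimate outcome in adolescents selected for being insufficiently active. It also depends on whether sessions displace other activity and on what group C does, so it is not simply adherence under another name.
- Part of the needed information is already planned. Adherence monitoring covers the number and length of sessions, and participants are asked at 6 and 12 weeks about other PA. However, nothing carries programme minutes into the PA outcome, and asking whether other PA was used does not yield minutes.
- The consultations are described as discussion. Calling them promotion of PA would go beyond the text.

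A reader might infer that the comparator contradicts itself, so that an obedient group C participant would have to ignore the pamphlet. The text does not support this, because the request exempts the assigned program and the article gives every participant one. A reader might also infer a built-in gain of 240 min/week in both active arms, or 240/420 = 57% of the eligibility ceiling (60 min × 7 days). That fails for yoga, whose minutes may not register on the log. The percentage also divides low or low-to-moderate minutes by a ceiling on moderate-to-vigorous activity.

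**Conclusion.** The point holds in a limited form. As written, a PA difference between group A or B and group C would largely reflect what was prescribed and how much of it was done. It could not by itself show a change in general PA. The session component is at most 240 logged min/week for dance at full adherence and possibly near zero for yoga. These figures assume that sessions are entered in the log and that the request is obeyed. The article does not settle the first, and the second will vary in practice.

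Group C's position is ambiguous, not contradictory. The ambiguity affects the by-group deviation count and the description of the comparator. The documents do not show that the pain, function or fatigue contrasts are damaged. That would require group C to be discouraged from using the pamphlet, which is nowhere stated.

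Severity is low to moderate. PA is one of several secondary outcomes in a 25-person pilot whose primary aims are feasibility and acceptability. The case for acting is that this concerns a participant instruction and a data-collection form, and minutes that were never separated may not be recoverable at the analysis stage.

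**What to change.** 1. In the existing weekly log, record programme-session minutes separately from all other PA.
2. Report total PA and non-programme PA side by side, with programme minutes as adherence. Whether non-programme PA should replace total PA as the sole outcome is a debatable choice of estimand and is not needed here.
3. State that the PAQ-A includes programme sessions and is not evidence of a change in general PA.
4. Reconcile the Group C section with both parts of Participant Allocation (the request and the group C procedures). Say that using the pamphlet is part of the assigned program in every group, and keep the request not to take up other exercise programmes.

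The cost is one extra log field and a few sentences. The PA contrast may become smaller if group C grows more active. The Results section says that recruitment and data collection had not started as of May 11, 2020, so at that date the change could be made before any data were collected.

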Create a new Facebook account: All participants will be asked to create an account specifically for the study and select a username that is meaningful to them but does not contain their first or last name, allowing them to remain anonymous.Access the group Facebook page: All participants will be invited to access the link to their group Facebook page, which they will be provided during their group assignment. Participants will be invited to follow the REDCap link provided on the Facebook page and answer baseline questionnaires about their participation in PA, pain, morning stiffness, functional status, fatigue, self-efficacy, and patient global assessment. This will take about 20 to 30 min to complete. The Facebook page will also contain the electronic pamphlet on PA (for all groups), the exercise videos (for groups A and B), and other information.

Following these steps, participants will be asked to complete the training program:

Groups A and B:

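### The week-0 patient-reported outcomes are answered after the participant knows her arm, so the analysed baseline is a post-randomisation, unblinded self-report, although it precedes training

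*Protocol article*

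**What the plan says.** All steps below are in the Protocol article, Methods, Participant Allocation, in the order in which that section gives them.

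1. Randomisation follows consent: "Once informed consent is obtained, participants will be randomly assigned to one of the 3 groups".
2. Allocation is disclosed, and the page link comes with it: "Participants will open the sealed opaque envelope containing their group assignment and a confidential link to access their Facebook group page".
3. An arm-specific briefing follows: "The research coordinator will explain the procedures related to the group assigned".
4. Under the baseline heading, participants create a study account and "access the link to their group Facebook page, which they will be provided during their group assignment".
5. From that page they reach the outcome questionnaires: "Participants will be invited to follow the REDCap link provided on the Facebook page and answer baseline questionnaires". The listed topics include physical activity (PA), pain, stiffness, function, fatigue and self-efficacy.
6. The same page carries intervention material: "The Facebook page will also contain the electronic pamphlet on PA (for all groups), the exercise videos (for groups A and B), and other information".
7. Training comes afterwards: "Following these steps, participants will be asked to complete the training program".

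The Data Analysis section takes assessment time at 0, 6 and 12 weeks as the within-subject factor of a repeated measures analysis of variance, so week 0 is an analysed response and not only a descriptive value.

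**The concern.** A baseline taken before allocation cannot depend on the arm except by chance. Here that protection is lost. The adolescent rates her own pain, fatigue and self-efficacy just after learning whether she received yoga, dance or the pamphlet, and after being asked which activity she prefers. Pleasure or disappointment may move her answers, and may affect whether she answers at all.

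Two things are at stake:

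- **The group-by-time contrast.** A shift at week 0 that is not matched at follow-up looks like a change over time in that arm. An upward shift in baseline pain in an exercise arm would look like benefit, and a downward shift would hide benefit.
- **Completeness by arm.** Someone who loses interest after opening the envelope is already randomised but has no baseline. Missing data and dropout are feasibility outcomes, so this loss would also enter the primary objective.

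**Working it through.** **1. Is there any other route to a pre-allocation baseline?** The places that might supply one are these:

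- *Recruitment*: a screening questionnaire precedes randomisation. At consent there is a sociodemographic and medical questionnaire plus a validated PA questionnaire. CHAQ function, fatigue and self-efficacy are not mentioned.
- *Participant Allocation, clinic questionnaire*: this covers pain level during regular activities and weekly PA, and it is described after the envelope steps. It is not the week-0 CHAQ pain measure. The two sections leave its timing relative to allocation unclear.
- *Participant Allocation, hospital webpage for those not using Facebook*: it carries information on the participant's own group, so it too follows allocation.
- *Outcome Measures, emailed link*: the same link goes to all three groups, with no statement that it is sent before allocation.

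None of these places the CHAQ, fatigue or self-efficacy baseline before allocation.

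**2. Sample size by arm (Study Design).** 25 × 2/5 = 10, 25 × 2/5 = 10 and 25 × 1/5 = 5. This reproduces the stated 10/10/5.

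**3. Bias formulas.** Let b0 and b1 be the shifts in one arm's reports, at baseline and at follow-up, caused by knowing the arm. Let s be the slope of follow-up on baseline. With no true effect:

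- bias of the change contrast = b1 − b0
- bias of the baseline-adjusted contrast = b1 − s × b0

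The documents give no b0, b1, s or SD. The values below are assumptions.

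| Scenario | Change contrast (absolute) | Adjusted contrast, s = 0.5 (absolute) |
|---|---|---|
| b0 = 5 mm, b1 = 0 | 5 mm | 2.5 mm |
| b0 = 10 mm, b1 = 0 | 10 mm | 5 mm |
| b0 = b1 = b | 0 | 0.5b |

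**4. Scale against sampling error.** Assume SD 20 mm and correlation 0.5. The SD of change is 20 × √(2 × 0.5) = 20 mm, and the standard error for 10 versus 5 is 20 × √(1/10 + 1/5) = 11.0 mm. A baseline-only shift of 5-10 mm is then 0.46-0.91 of a standard error.

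**5. Simulation of the baseline-only case** (10 versus 5, SD 20 mm, correlation 0.3 to 0.7, 40,000 replicates, no true effect, two-sided 5% test of change):

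| Baseline shift | Rejection rate | Adjusted-contrast bias (absolute) |
|---|---|---|
| 0 mm | 4.9-5.0% | about 0 |
| 5 mm | 6.6-8.4% | 1.5-3.5 mm |
| 10 mm | 10.9-20.0% | 3.0-7.0 mm |

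**6. Loss.** One participant without a baseline is 1/10 = 10% of group A or B and 1/5 = 20% of group C. Two are 20% and 40%.

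**The case against.** The order of steps is hard to dispute. The objections concern size and weight, and most of them stand.

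- **The bias depends on an unequal shift.** The same unblinded participants report at every visit. If knowing the arm moves all their reports equally, the change score is unbiased as the plan stands. With a pre-allocation baseline (b0 = 0), both contrasts would carry the follow-up shift b. So 5-10 mm is one scenario, and re-ordering does not reduce bias in all of them. This stands. However, the cancellation needs two shifts twelve weeks apart to be equal, which the trial cannot check.
- **The outcomes are secondary.** The primary objectives are feasibility and acceptability, and the sample size is justified by feasibility and variance estimation. No decision rule rests on week 0. This stands.
- **Loss is mitigated.** A gift certificate is paid for the baseline questionnaires, the link is emailed with reminders, and dropout is recorded by group with reasons. A mixed model, which the plan will consider, can keep a participant who lacks week 0. These points lower the risk without removing it.
- **Unblinding is disclosed.** The article admits that participants are not blinded and that self-report may be biased. It does not discuss when baseline is taken. The anonymous questionnaires and blinded analyst do not help, because the respondent is the assessor.

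A reader might infer that baseline is contaminated by the intervention itself, or that the pilot's main conclusions are invalid. The documents support neither: baseline precedes training, and the main conclusions concern feasibility and acceptability. Nothing bars a participant from watching a video first, but that is an opportunity and not a shown exposure.

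**Conclusion.** The point holds as a design weakness that should be fixed. It does not invalidate the pilot. As written, week-0 CHAQ pain and function, stiffness, fatigue, self-efficacy and the PAQ-A are answered with the arm known and its page open. For PA, part of the information may be collected earlier in clinic, and its timing needs stating.

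The size is conditional. A baseline shift of 5-10 mm in one arm, not matched at follow-up, biases the change contrast by up to 5-10 mm and an adjusted contrast by the slope times that. An equal shift at all visits gives no bias in the change score. The shift is an assumption throughout, so this is a plausible risk and not a demonstrated effect. For completeness, a single missing baseline costs 20% of group C if the analysis cannot use her later data.

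**What to change.** Have participants complete the week-0 questionnaires through an arm-neutral REDCap link after consent and before randomisation, or at least before the envelope is opened. Release the envelope only when REDCap shows baseline complete. State that the clinic PA and pain questionnaire also precedes allocation, so that Recruitment and Participant Allocation agree.

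This restores a baseline that is independent of the arm and ensures that every participant who learns her allocation has one. It does not remove reporting bias at 6 and 12 weeks, which remains an open-label limitation to acknowledge.

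The cost is a clinic visit 20-30 minutes longer (the article's own estimate for the questionnaires) or a short delay before allocation, plus a wording change notified to the ethics board. The article reports that recruitment had not started as of May 11, 2020, and on that status no collected data are affected.
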